### Sample size (Phases 1 and 2)

The sample will consist of magistrates and public servants from the judiciary who score a minimum of 7 points on the recruitment instrument (SRQ-20), which is available for online completion throughout the regional jurisdiction via an electronic platform integrated into TRT5’s intranet.

The sample size for Phase 1 of the study was determined with Soler et al. [23] as a reference, considering a minimum of 30 participants. For Phase 2, the study primarily referred to a meta-analysis conducted by Khoury et al. [39], which assessed the effectiveness of 8-week mindfulness-based interventions in healthy individuals and found an average dropout rate of 10 %.

To establish statistical significance, a sample size of 72 individuals was estimated using G*Power 3.1.9.2, based on a one-tailed *t*-test for independent samples with α=0.05, β=0.20, and Cohen's *d* = 0.6. Considering an approximate dropout rate of 25 %, which is higher than that found in similar studies, an estimated recruitment of approximately 90 eligible individuals for the intervention and control groups is anticipated.

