Randomization success will be determined by no significant differences between the groups regarding demographic and clinical characteristics. Continuous variables will be analyzed using Student's *t*-test, and categorical variables will be analyzed using chi-square or Fisher's exact tests. Longitudinal data (T0, T1, and T2) for both intervention and passive control (waitlist) groups will be tracked using the repeated measures Student's *t*-test. Spearman's correlation test will assess variable correlations. M-TBCT program efficacy will be evaluated using repeated measures ANOVA to examine the main effects of time and treatment and their interaction. McNemar's test will assess changes in mental disorder risk classification after M-TBCT intervention. Effect sizes (Cohen's d) and 95 % CI will be calculated for intra- and inter-group comparisons (intervention and waitlist). The Bonferroni correction will be applied to adjust for various statistical tests.

The data will be analyzed through intention-to-treat (ITT), including all randomized participants in their initially assigned group, regardless of completing the treatment protocol. Per-protocol analysis will exclude participants with fewer than four sessions (50 % of the M-TBCT program). Attrition analysis (As-treated) will compare those who completed the protocol with those who responded only to the initial questionnaire. This study employs mixed-effects linear models (MLMs) for statistical analysis. Fixed variables, including depression, anxiety, and self-care, will be incorporated, whereas random variables will be introduced to capture intra-individual variation over time. This will enable modeling of unexplained individual differences not accounted for by the fixed variables, providing a robust approach to understanding the relationships between these variables and well-being throughout the study.

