Mediation analysis will be employed to examine the potential interaction among variables, notably depression (PHQ-9), anxiety (GAD-7), cognitive distortions (CD-QUEST) and self-care (ASAS-R), and the primary outcome, represented by well-being (WHO-5). These independent variables will be assessed for their direct impact on well-being, while sociodemographic variables such as gender, age, socioeducational level, income, marital status, number of children, occupation, and working hours will be treated as covariates in the mediation analysis to control for potential confounding factors. All statistical analyses will be conducted using SPSS 28.0 software, with a significance level of 5 % for all study hypotheses.

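### The named efficacy test, repeated measures ANOVA, keeps only participants with all three scores, which does not fit the promised intention-to-treat analysis of everyone randomised

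*Protocol article*

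**What the plan says.** All the analysis statements are in the protocol article under Statistical methods (Phases 1 and 2).

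- **Efficacy test:** "M-TBCT program efficacy will be evaluated using repeated measures ANOVA to examine the main effects of time and treatment and their interaction". The section gives the longitudinal data as T0, T1 and T2, and Evaluation measures places the last of these at six months.
- **Analysis population:** "The data will be analyzed through intention-to-treat (ITT), including all randomized participants in their initially assigned group, regardless of completing the treatment protocol". A separate per-protocol set leaves out people with fewer than four sessions.
- **Second longitudinal model:** "This study employs mixed-effects linear models (MLMs) for statistical analysis". Its content is described as "Fixed variables, including depression, anxiety, and self-care, will be incorporated, whereas random variables will be introduced to capture intra-individual variation over time", and its aim as "providing a robust approach to understanding the relationships between these variables and well-being throughout the study".
- **Software:** "All statistical analyses will be conducted using SPSS 28.0 software".

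Sample size (Phases 1 and 2) derives 72 participants and then allows for about 25% dropout, "which is higher than that found in similar studies, an estimated recruitment of approximately 90 eligible individuals".

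**The concern.** The SPSS repeated measures procedure needs one full row per person. Someone with T0 and T1 but no six-month score is removed from the whole analysis, including the part that concerns the change from T0 to T1. The population analysed is then people with three completed questionnaires, not everyone randomised, although the result would carry the intention-to-treat label.

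This matters for two reasons. Returning all three forms happens after randomisation, and participants know their arm because they are told either to start or to wait (Implementation). Outcomes are self-reported, and waitlisted people are offered the intervention only after the study and only if results are favourable. Return of forms could therefore differ by arm in a way linked to well-being. In addition, valid T1 scores, which measure the effect straight after the eight sessions, would not be used in the efficacy test.

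**Working it through.** **1. Reproduce the planned sample size.** Inputs from Sample size: one-sided α = 0.05, power 0.80, d = 0.6, two equal groups. Power = P(T > t_crit), where T is noncentral t with df = n1 + n2 − 2 and noncentrality d × √(n1·n2/(n1 + n2)).

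With 36 per arm: noncentrality = 0.6 × √18 = 2.546, df = 70, t_crit = 1.667, power = 0.809. The stated 72 is reproduced. The stated 90 is 72 × 1.25.

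**2. Count who remains in the ANOVA.** The article gives 25% as dropout and does not say what share will lack a questionnaire. *Assumption:* 25% of the 90 lack at least one of the three scores.

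Complete records = 90 × 0.75 = 67.5, that is, 67 to 68 people. Left out = 90 × 0.25 = 22.5, that is, 22 to 23 people.

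**3. Power of the planned t-test at that size.** With 33.75 per arm: noncentrality = 0.6 × √16.875 = 2.465, df = 65.5, t_crit = 1.668, power about 0.79. This is the power of the t-test used for planning, not of the ANOVA interaction, for which the article gives no inputs.

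Range over the assumed share with any missing score:

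| Share with a missing score | Analysed | One-sided power |
|---|---|---|
| 10% | 81 | 0.849 |
| 20% | 72 | 0.809 |
| 25% | 67–68 | about 0.79 |

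**4. Observed T1 scores left out.** This depends on how many people miss T1 itself, which the article does not give. *Assumption:* anyone who misses T1 also misses T2, with 25% missing by T2.

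- If 10% lack T1, then 90 × 0.90 = 81 have it, and 81 − 67.5 = 13.5, so 13 to 14 observed T1 scores are unused.
- If all the loss occurs before T1, none is unused.
- If all the loss occurs after T1, 22 to 23 are unused.

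**5. Does the mixed model carry the efficacy test?** The ANOVA sentence assigns efficacy by name and lists time, treatment and their interaction. The mixed-model sentences name depression, anxiety and self-care as fixed variables and give as their purpose how these relate to well-being. Neither arm nor time is named. Read as written, this is an association model. If it were used for efficacy with those variables entered as measured over time, it would adjust the arm effect for outcomes that the treatment is itself meant to change.

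**The case against.** **Missing-data handling may be set out elsewhere.** The article condenses a fuller protocol, and an analysis plan may exist. A stated imputation would let the ANOVA include everyone. This is a fair limit: the absence of an imputation rule is not the point. What stands is that the article names a test and a population that do not fit each other when the test is run as named.

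**The mixed model may be the intended intention-to-treat analysis.** Its opening sentence is unrestricted, it sits in the same paragraph as the intention-to-treat promise, and its list of fixed variables is introduced as non-exhaustive. The text is therefore open to that reading. Even so, efficacy is assigned elsewhere by name, so the article needs to say which model is primary.

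**Dropping out of sessions is not the same as missing a form.** This is correct. Questionnaires are online and asynchronous, so people who stop attending can still answer. The count of 67 to 68 is conditional for that reason.

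**T1 data are not lost to the study.** This is also correct. Between-group effect sizes and paired t-tests are planned too, and nothing limits those to people with a six-month score. The omission concerns the ANOVA only.

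**Stronger readings that the documents do not support.** A reader might infer that the completers' analysis inflates the false-positive rate by a known amount. Simulations with 45 per arm, no true effect and assumed correlations (T0–T1 0.5, T1–T2 0.6, T0–T2 0.45) gave no bias and 5.0% rejection when low scorers left equally in both arms. They gave about 0.18 SD and 11–12% when low scorers left one arm and high scorers the other. The article offers nothing with which to choose between these. A reader might also take 40% loss from the 60% retention criterion, but that is a Phase 1 feasibility threshold and not a Phase 2 expectation.

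**Conclusion.** The point holds in a limited form. As published, the efficacy test and the promised analysis population are inconsistent unless missing scores are filled in, and the mixed model as described does not close the gap.

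If 25% lack a visit, about a quarter of those randomised would be absent from an analysis labelled intention-to-treat. The power cost against plan is negligible, so power is not the reason to change. The reasons are the mislabelled population, the unused T1 scores, and a possible bias whose direction and size cannot be settled from the article. If missingness is unrelated to outcome, or related to it in the same way in both arms, little or no bias is expected.

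Severity: should-fix. That the ANOVA drops incomplete cases follows from the method named. Every figure on loss rests on the assumptions shown above.

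**What to change.** Name one primary efficacy analysis: a likelihood-based mixed model of WHO-5 with visit and arm-by-visit terms and baseline accounted for, using all available scores from every randomised participant. Do not enter depression, anxiety, cognitive-distortion or self-care scores measured after randomisation as covariates. Report the arm differences at T1 and at six months from this model. Add a sensitivity analysis for data not missing at random. Keep the model that relates symptoms and self-care to well-being as a separate, exploratory analysis. If the repeated measures ANOVA stays, call it a completers' analysis. The covariance structure and the way baseline is handled can be left to the analysis plan.

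**Cost:** wording, and a little more analysis work. SPSS and mixed models are already named, and no new data are needed. The model still assumes that data are missing at random given the observed scores, which is why the sensitivity analysis is needed.

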### Hypotheses

Based on prior research, we hypothesize:

Hypothesis 1 (H1)M-TBCT will demonstrate acceptance and feasibility among judges and public servants in the judiciary.

Hypothesis 2 (H2)M-TBCT will significantly improve psychological well-being, self-care, and reduce anxiety, depression and cognitive distortions compared to the control group.

Hypothesis 3 (H3)The benefits of M-TBCT will be maintained at the six-month follow-up.

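### The Bonferroni rule names no family or divisor and does not exempt WHO-5, so the threshold for the primary test is not fixed; if WHO-5 is in the family, the sample size gives less than 80% power

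*Protocol article*

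**What the plan says.** Three statements in the protocol article bear on the significance threshold.

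- **Statistical methods (Phases 1 and 2), adjustment:** "The Bonferroni correction will be applied to adjust for various statistical tests". The sentence closes a paragraph that covers baseline comparisons, repeated-measures t-tests, Spearman correlations, the repeated-measures ANOVA for efficacy, McNemar's test and effect sizes. It says neither which of these form the family nor how many tests alpha is divided by.
- **Same section, final sentence:** the analyses are run "with a significance level of 5 % for all study hypotheses". It does not say whether the 5% holds per test or over a family.
- **Sample size (Phases 1 and 2):** "a sample size of 72 individuals was estimated using G*Power 3.1.9.2", "based on a one-tailed" t-test with "α=0.05, β=0.20, and Cohen's" d of 0.6. No share of alpha is set aside for multiplicity.

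Two other sections matter. The Results section names WHO-5 as the primary outcome and PHQ-9, GAD-7, CD-QUEST and ASAS-R as secondary. The Hypotheses section joins all five in H2: "M-TBCT will significantly improve psychological well-being, self-care, and reduce anxiety, depression and cognitive distortions compared to the control group". Nothing states that WHO-5 is tested first or stands outside the Bonferroni adjustment.

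**The concern.** The article commits to a multiplicity method, a significance level and a sample size, and the three together do not determine the threshold that WHO-5 must meet. Read literally, the Bonferroni sentence covers the efficacy tests along with the rest, so the single primary outcome would give up alpha to tests that need not compete with it. The sample size made no allowance for that. Read more narrowly, Bonferroni applies only to secondary or follow-up comparisons and WHO-5 keeps the full 5%.

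The stakes are practical. A WHO-5 p-value between 0.05/k and 0.05, where k is the number of tests in the family, is positive on one reading and negative on the other. As written, the choice between the two could be made after the data are seen.

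**Working it through.** **Inputs.** From Sample size (Phases 1 and 2): d = 0.6, one-tailed alpha = 0.05, beta = 0.20, 72 in total. From Randomization and blinding: 1:1 allocation, so 36 per arm. The article gives no k. I show k from 1 to 10 as an assumption: k = 5 is the number of outcomes in H2, and k = 10 would be those five at two post-baseline assessments.

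**Formulas** (independent-samples t-test, noncentral t):
- noncentrality δ = d × √(n₁n₂/(n₁+n₂)) = 0.6 × √(36 × 36/72) = 0.6 × √18 = 2.546
- critical value t* = upper 0.05/k point of t on 70 df
- power = P(T > t*), with T noncentral t on 70 df and noncentrality δ
- smallest significant observed effect = t* × √(2/36) = t* × 0.2357

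**Step 1: reproduce the plan's figure.** At k = 1, t* = 1.667 and power is 0.809. The smallest n per arm that reaches 0.80 is 36, so the total is 72, as stated. The figure therefore rests on an undivided one-tailed 0.05.

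**Step 2: put WHO-5 inside a family of k tests.**

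| k | alpha per test | power, 36 per arm | power, 45 per arm (all 90 analysed) | smallest significant d, 36 per arm | total analysed for 80% |
|---|---|---|---|---|---|
| 1 | 0.05 | 0.809 | 0.881 | 0.393 | 72 |
| 2 | 0.025 | 0.709 | 0.804 | 0.470 | 90 |
| 3 | 0.0167 | 0.647 | 0.752 | 0.512 | 102 |
| 5 | 0.01 | 0.567 | 0.683 | 0.561 | 116 |
| 10 | 0.005 | 0.464 | 0.586 | 0.624 | 134 |

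**Step 3: size of the undecided zone.** With k = 5, a WHO-5 result with 0.01 < p < 0.05 (observed d between 0.393 and 0.561) changes verdict with the reading. If the true effect is 0.6, the chance of landing there is the difference in power, 0.809 − 0.567 = 0.242. With k = 10 it is 0.809 − 0.464 = 0.345.

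**Step 4: put WHO-5 outside the family.** This is k = 1: power stays at 0.809 and the sample size is consistent with the test.

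**The case against.** The strongest case is that nothing here conflicts. Bonferroni needs an overall level to divide, and 5% can be that level. The article names one primary outcome, and the undivided alpha in the sample size fits a reading in which WHO-5 is not adjusted. Naming the family is also a detail that an article may leave to the analysis plan.

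Much of this stands, and it rules out several stronger claims that a reader might infer:

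- *The two sentences contradict each other.* They do not: a 5% familywise level split by Bonferroni satisfies both. The fault is that the threshold is left open.
- *Bonferroni removes the stated power.* Only if WHO-5 is in the family, which the article neither says nor excludes.
- *The assumed effect of 0.6 would itself miss significance at k = 5.* That requires a two-sided test. Under the one-tailed test used for the sample size, the smallest significant d at k = 5 is 0.561, so an observed 0.6 would pass.
- *H2 could be claimed on one chance finding among five scales.* H2 is worded as a conjunction; as written it needs all five, and requiring all five at 5% does not inflate the error of that claim.
- *Reporting 95% intervals beside adjusted tests is an error.* It is common practice and breaks no stated rule.

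The appeal to an analysis plan does not remove the point. A plan that put WHO-5 in the family would depart from the alpha behind the sample size; one that left it out would have to narrow a sentence that carries no qualification. Either way a statement in the article needs correcting.

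**Conclusion.** The multiplicity rule is badly fixed. The Bonferroni family and divisor are undefined, the primary outcome is not exempted, and the 5% is not said to be familywise or per test. For WHO-5 the planned 72 give power of 0.81 if it is outside the family, and about 0.57 (k = 5) or 0.46 (k = 10) if it is inside.

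These figures rest on the article's own sizing model: one-tailed t-test, d = 0.6, 36 analysed per arm. The values of k are assumed. Efficacy is to be tested by repeated-measures ANOVA, whose power depends on a within-person correlation that the article does not give, so the figures show the scale of the problem and not the power of the final analysis.

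This is an inexpensive improvement to make before the data are analysed. It is not a flaw that undermines the trial.

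**What to change.** Replace the two sentences in Statistical methods with one rule:

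1. WHO-5, in one named primary between-group contrast, is tested alone at the full alpha used in the sample size, with no Bonferroni share.
2. Only if that test is significant, PHQ-9, GAD-7, CD-QUEST and ASAS-R are tested with Holm at an overall 5%.
3. The within-arm tests, correlations, McNemar's test and mediation analysis are exploratory and outside the family.

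This keeps the basis of the 72, and for the primary outcome it is more powerful than a Bonferroni split over all tests. Other orderings would also serve, provided that the rule is written down and WHO-5 keeps the alpha it was sized for.

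The change is wording only, with no additional participants or data. The one small downside is that confirmatory claims on the four secondary scales depend on WHO-5 being significant.

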### Ethical considerations

This study is currently under review by the Research Ethics Committee involving Human Subjects at the Federal University of São Paulo (CAAE: 73,817,423.3.0000.5505). Upon approval, the study will be registered with the Brazilian Clinical Trials Registry (REBEC), which is available at https://ensaiosclinicos.gov.br/.

## Protocol validation

### Discussion

To the best of our knowledge, this study represents a novel approach for integrating mindfulness and TBCT into a structured protocol specifically for the judiciary. Addressing the high prevalence of mental disorders in this sector, which is a leading cause of work-related absenteeism, our protocol aims to offer suitable psychotherapeutic solutions to enhance the well-being of judges and public servants.

We anticipate that our study will contribute substantially to scientific knowledge, guiding the selection and implementation of effective mental health interventions within healthcare systems, particularly in occupational settings such as the judiciary. The study's findings are expected to promote a culture of autonomy and self-efficacy, which are crucial for enhancing well-being, self-care, and productivity .

It is worth mentioning that Peuker et al. [43] emphasized the importance of seeking scientific evidence and its articulation in clinical practice. According to her, this articulation enables the appropriate provision of health demands in various contexts, generating positive impacts on the public system. These impacts often result from the implementation of interventions that are viable, well-accepted, and effective for their intended purposes.

The integration of MBHP and TBCT in M-TBCT is a novel approach particularly suited to the judiciary sector, where the nature of work can lead to unique psychological challenges. The judiciary's high-stress environment and the critical nature of the work undertaken by judges and public servants make this sector a critical area for the implementation of effective mental health interventions [[44], [45], [46]].

Furthermore, the online delivery format of M-TBCT is particularly pertinent in the context of the recent global shift toward remote work and digital health care solutions, a trend accelerated by the COVID-19 pandemic. This mode of delivery could overcome barriers to accessing mental health care in the judiciary, such as time constraints and stigma [47].

Given the efficacy of MBHP and TBCT in various settings and the unique demands of the judiciary sector, M-TBCT could offer a valuable tool for improving mental health and well-being among judiciary professionals. The proposed study will contribute to the literature by exploring the acceptability, feasibility, and effectiveness of this integrated approach in a new context, potentially providing a model for similar interventions in other high-stress professional environments.

### Limitations

On the other hand, while pioneering in its approach and methodology, this study is subject to several limitations that should be considered when interpreting its future results [48,49]:1.**Online Intervention Format**: The intervention will be delivered online, which, while advantageous in terms of accessibility, may can influence participant engagement and the efficacy of the therapy. Differences in digital literacy, internet access quality, and the absence of face-to-face interaction could impact the outcomes.2.**Sample Specificity**: The study focuses on judges and public servants within the judiciary, which may limit the generalizability of the findings to other professional groups or sectors. The unique stressors and work environment of the judiciary might mean the intervention's effectiveness could vary in different contexts.3.**Self-Report Measures**: The reliance on self-report measures for assessing psychological well-being and mental health symptoms could introduce biases such as social desirability or self-assessment inaccuracies. Objective measures, if available, could complement these findings.4.**Control Group Design**: While a controlled and randomized design will be used, the nature of the control group and potential differences in their experiences compared to the intervention group might influence the study's results.5.**Short-Term Follow-Up**: The follow-up period of this study is relatively short-term. Long-term effects of the intervention, which are crucial for understanding its sustainability and enduring impact, remain unknown.6.**Potential Confounders**: There might be unmeasured confounding variables that could affect the outcomes, such as personal life stressors, varying levels of work pressure, or pre-existing mental health conditions.

These limitations highlight the need for further future research in this area, including long-term studies with diverse populations and varied intervention formats, to further validate and extend the findings of this study.

